### 3.10. Limitations of Economic Evaluation

Several limitations of the exploratory cost analysis should be acknowledged. First, the use of historical controls rather than a concurrent randomized comparator introduces potential for confounding, though propensity score matching will mitigate this. Second, the small sample size limits the precision of cost-effectiveness estimates; results should be interpreted as preliminary evidence to inform future definitive economic evaluations. Third, the 24-week time horizon may not capture the full economic consequences of the intervention if benefits or costs accrue over longer periods. Fourth, the healthcare system perspective excludes productivity losses and informal caregiving costs that may be relevant from a societal perspective. These third and fourth concerns are partly addressed by the secondary long-term Markov extrapolation and the additional societal-perspective analysis described above, which incorporate longer time horizons, productivity losses, and informal caregiver costs; the extrapolated estimates nonetheless remain dependent on modeling assumptions and should themselves be regarded as exploratory. Despite these limitations, this economic evaluation will generate important preliminary evidence to support decision-making regarding BCI technology adoption in stroke rehabilitation.

### 3.11. Implementation Science Framework

Implementation outcomes will be evaluated using the RE-AIM framework (Reach, Effectiveness, Adoption, Implementation, Maintenance), a well-established model for assessing the translation of research interventions into clinical practice [49,50]. This framework enables comprehensive evaluation of factors critical to sustainable implementation of BCI rehabilitation in routine clinical settings (Table 3).

### 3.12. Data Analysis

Data analysis will be performed using Python (version 3.11; Python Software Foundation, Wilmington, DE, USA) programming language with established statistical packages. Descriptive statistics will be expressed as mean and standard deviation (SD) for normally distributed continuous variables or median with interquartile range (IQR) for non-normally distributed data. Given the small sample size characteristic of feasibility studies, non-parametric tests, including the Wilcoxon signed-rank test, will be employed for within-subject comparisons across time points. *p*-values will be corrected for multiple comparisons using the Benjamini–Hochberg False Discovery Rate (FDR) correction, with statistical significance set at alpha = 0.05 [51].

Pre-specified stratified and subgroup analyses will be undertaken. Given potentially divergent recovery trajectories between ischemic and hemorrhagic stroke, feasibility metrics and clinical outcomes will be reported separately for the ischemic and hemorrhagic subgroups, and where cell sizes permit, differences will be explored using exploratory between-subgroup comparisons (Mann–Whitney U tests for continuous outcomes and Fisher’s exact tests for proportions). Outcomes will likewise be summarized by baseline FMA-UE severity stratum (severe, 0–19; moderate-to-mild, 20–47) and, descriptively, by lesion location (cortical, subcortical, brainstem, or cerebellar). Because the feasibility sample (*n* = 12) is not powered for subgroup inference, all stratified analyses are explicitly exploratory and hypothesis-generating; they are intended to estimate the direction and variability of effects by stroke etiology and severity, will be reported with effect estimates and confidence intervals rather than an emphasis on *p*-values, and will inform pre-registered subgroup hypotheses for the future definitive trial.

Based on preliminary data from our meta-analysis of BCI rehabilitation in chronic stroke [24], we expect to observe improvements in FMA-UE scores with a mean change of approximately 5.23 points (standard error 0.70) by the end of 15 training sessions. Historical data from TTSH indicate a mean FMA-UE improvement from 29.1 to 37.4 points (+8.3 points) with standard rehabilitation [40]; thus, BCI may yield an expected total improvement of approximately 13–14 points if effects are additive.

**Interim Analysis:** An interim review will be conducted after enrollment of the first five patients. The interim analysis will evaluate eligibility verification (100% target), informed consent documentation (100% target), serious adverse event rate (0% target), adverse event rate related to training (≤17% target), and dropout rate (less than 20% during training phase). Continuation, modification, or termination of the study will be determined based on these interim metrics.

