Brain–computer interface (BCI) addresses this lack of a closed-loop system connecting volitional intent with limb movement [11,12]. BCI records neural signals, decodes motor intents, and uses decoded signals to control either external devices (end effector robots or neuroprostheses or virtual reality (VR platforms), or internal effectors (functional electrical stimulation of the patient’s muscles [13,14], thus reestablishing volitional control of their paretic limbs through motor imagery via electroencephalographic (EEG) signal decoding or MI-EEG feedback [15] and restoring temporal dependence between cortical (presynaptic) and end effector (postsynaptic) neurons. The resulting successful MI-EEG triggering the end-effector limb movement in turn generates ascending sensory perception, completing a closed-loop biofeedback system that reinforces motor learning [16,17].

Recent systematic reviews and meta-analyses have demonstrated that BCI-based rehabilitation produces clinically and statistically significant improvements in upper extremity motor function [18,19,20]. Locally, Ang et al. (2011) conducted a large clinical study demonstrating that stroke patients could successfully use EEG-based motor imagery BCI, establishing feasibility in this population [21]. Subsequent research by Várkuti et al. (2013) showed that resting state changes in functional connectivity correlated with movement recovery following BCI and robot-assisted upper-extremity training [22]. Ang et al. (2015) in two randomized controlled trials comparing duration-matched controls with either RAT or BCI-RAT paired with either shoulder–hand or wrist–hand end-effector robots, demonstrated the efficacy of MI-EEG-RAT in chronic stroke patients with significant pre/post-training effects without significant inter-group differences between conventional UE rehabilitation controls, robotic only, and BCI-RAT intervention groups [21,23]. Furthermore, BCI-RAT groups were associated with high levels of safety, and within group impairment reductions were sustained till week 24 follow-up, thus providing an important foundation for extending BCI research into the subacute/chronic stroke inpatient populations [21,23].

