Existing studies, however, involved predominantly chronic stroke patients. In our recent meta-analysis of predominantly chronic stroke cohorts, BCI rehabilitation produced a mean improvement of 5.23 points on the Fugl–Meyer Assessment Upper Extremity (95% confidence interval 3.85 to 6.61; total score range 0 to 66, with higher scores indicating less impairment), exceeding the established minimal clinically important difference of 4 to 6 points for the FMA-UE [24]. We hypothesize that there may potentially be greater benefits when BCI is applied during the acute/subacute phase when neuroplasticity is heightened. Notably, an overview of systematic reviews by Liu et al. (2025) concluded that BCI-combined treatment improves upper limb motor function and quality of daily life, with effects particularly pronounced in the subacute phase [25]. In acute and subacute stroke, several studies have alluded to moderate quality evidence and high safety profile and efficacy of BCI when coupled with end effectors such as FES, VR, or robots, achieving mean FMA-UE difference of 3.69–5.02 albeit with less robust gains for ADL independence. Subgroup analyses indicated that interventions < 30 days of stroke for <3 weeks may yield greater benefits, in particular paired with FES. Optimal training parameters suggested daily sessions of 20–90 min or 2–5 times weekly for 3–4 weeks [26,27] (Figure 1).

However, practical implementation of BCI technology within acute inpatient hospital settings presents logistical challenges and must also be carefully evaluated. The setup of EEG headsets with wet electrodes requires trained personnel and can add at least 10–15 min of preparation time per session, including set-down and scalp cleansing after MI-BCI to achieve adequate electrode impedance [28,29].

Lastly, economic data remain scarce, creating barriers to widespread implementation in healthcare systems [30]. Understanding the incremental cost-effectiveness of BCI rehabilitation compared to standard care is essential for informing policy decisions regarding technology adoption and reimbursement. This study therefore incorporates a prospective economic evaluation alongside the clinical feasibility assessment to generate preliminary cost-effectiveness evidence.

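### Section 3.12 states two incompatible expected FMA-UE gains, reaches the larger by adding a within-patient change to the standard-care gain, and names only a test against zero change

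*Protocol article*

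**What the plan says.** The last paragraph of Section 3.12 (Data Analysis) makes three statements in sequence.

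- It takes its starting figure from chronic stroke: "Based on preliminary data from our meta-analysis of BCI rehabilitation in chronic stroke". From this it expects a "mean change of approximately 5.23 points (standard error 0.70) by the end of 15 training sessions".
- It reports local experience without BCI: "mean FMA-UE improvement from 29.1 to 37.4 points (+8.3 points) with standard rehabilitation".
- It adds the two: "thus, BCI may yield an expected total improvement of approximately 13–14 points if effects are additive".

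The same section names the method for change over time: "non-parametric tests, including the Wilcoxon signed-rank test, will be employed for within-subject comparisons across time points". Significance is set at 0.05 after Benjamini–Hochberg correction. Section 2.5 lists clinical efficacy as secondary hypothesis (i), naming FMA-UE, ARAT, FIM and MBI without a success criterion. Under Section 2.6 (Concomitant Therapy), every BCI session is followed by 60 minutes of standard occupational therapy.

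The Discussion concedes that gains cannot be definitively attributed to BCI rather than spontaneous recovery. It plans to compare FMA-UE and ARAT trajectories with matched historical controls and published recovery models.

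**The concern.** There are three linked problems.

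**Two expectations for one quantity.** Participants receive BCI and standard therapy together, so the trial will observe a single FMA-UE change. The paragraph expects that change to be about 5.23, and then about 13–14. The first value is below the 8.3 that the same paragraph credits to standard rehabilitation without BCI.

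**The wrong kind of quantity is added.** A within-patient change already contains whatever concurrent therapy or recovery contributed in the source cohorts. It can be added to a standard-care gain only if that contribution was nil. Making the sum conditional on additivity does not repair this, because additivity concerns increments over a comparator.

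**The named test has an uninformative reference.** Rejecting zero change shows that patients improved. It does not show that they improved more than under the standard rehabilitation they also received. A significant result could be read as clinical efficacy when BCI contributes nothing.

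**Working it through.** **Inputs**

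- BCI change: 5.23 points, SE 0.70 (Section 3.12); "95% confidence interval 3.85 to 6.61" (Section 1).
- Standard-care gain: 29.1 to 37.4 (Section 3.12).
- SD of 3.4 for the paired calculation; 4-point between-group difference at SD 6 for a future two-arm trial; n = 12, or 10 after dropout (Section 2.4).
- Acute/subacute evidence: "achieving mean FMA-UE difference of 3.69–5.02 albeit with less robust gains for ADL independence" (Section 1).
- No SD of change is given for this population. The range 3.4 to 12 is assumed; 3.4 and 6 are the two SDs that appear in Section 2.4.

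**1. Reproduce the stated total.** 37.4 − 29.1 = 8.3, and 8.3 + 5.23 = 13.53, so 13–14 is a plain sum. Over the confidence interval for 5.23 it runs from 8.3 + 3.85 = 12.15 to 8.3 + 6.61 = 14.91. The arithmetic is right.

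**2. What kind of figure is 5.23?** Section 2.4 uses it, with SD 3.4, to support a paired within-group sample size. A noncentral-t calculation at that SD (two-sided 0.05, power 0.80) gives n = 5, 6 and 8 for changes of 6, 5.23 and 4 points, close to the stated 6–8. The Figure 1 legend describes each patient's change after BCI therapy, drawn from the same meta-analysis. Both uses are within-patient.

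**3. Why the sum fails.** Write the within-patient change as d + c, where d is the increment due to BCI and c is everything else that moved the score in those cohorts. The expected total here, if increments add, is 8.3 + d. The protocol computes 8.3 + d + c. The two agree only if c = 0.

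**4. What a between-group input would give.**

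- 8.3 + 4 = 12.3, using the protocol's own planning difference.
- 8.3 + 3.69 = 11.99 and 8.3 + 5.02 = 13.32, if that range is a difference versus control.

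These lie 1.23, 1.54 and 0.21 points below 13.53.

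**5. What the test against zero would show if BCI added nothing.** Exact two-sided Wilcoxon signed-rank test at 0.05, normal changes with true mean 8.3, 40,000 simulated samples per cell, no FDR correction:

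| Assumed SD of change | n = 12 | n = 10 |
|---|---|---|
| 3.4 | 100% | 100% |
| 6 | 98.5% | 96.5% |
| 8 | 87.6% | 81.3% |
| 10 | 69.8% | 63.1% |
| 12 | 54.2% | 48.2% |

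**6. The same test with 8.3 as the reference, n = 12.** With no BCI effect, it rejects in about 4% of trials. If the full 13.53 were true, it would reject in 99.6%, 74%, 49%, 34% and 25% of trials for SDs of 3.4, 6, 8, 10 and 12. These figures treat 8.3 as known without error, so a real comparison with historical controls would do less well.

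**The case against.** The strongest reply is that efficacy is secondary and the protocol is open about its limits. Section 2.4 says the aim is to estimate feasibility parameters. Section 2.6 admits confounding by therapy dose and plans therapy time as a covariate. The Discussion plans the matched-control benchmark plus sensitivity analyses that assign part of the gain to spontaneous recovery. Zero is therefore not the only reference in the document. This stands, and it limits the weight of the point. What remains is that Section 3.12 does not carry the benchmark through. It plays down p-values for the stratified analyses but not for the main pre–post tests.

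A second reply is that the protocol describes chronic patients as having stopped improving under usual therapy, so c in step 3 could be small. That is arguable. However, the Background also cites chronic-stroke trials with "significant pre/post-training effects without significant inter-group differences between conventional UE rehabilitation controls, robotic only, and BCI-RAT intervention groups". A lack of significant difference does not prove equality, but it is a poor basis for assuming that the whole within-patient change is increment.

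A reader might also infer more than the document supports:

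- *That 13–14 inflates the definitive trial.* It does not: Section 2.4 plans on a 4-point difference, and the Discussion says the future trial will be powered on the minimal clinically important difference and the variance observed here. The figure enters no sample size, interim rule or feasibility benchmark.
- *That a significant Wilcoxon result is the declared criterion for efficacy.* No such rule is stated.
- *That a cohort gaining 5–6 points would have done worse than local care.* The period over which the 8.3 accrued is not given, so this does not follow for week 3–4.
- *That standard care would certainly beat zero.* At SD 12 the probability is about one half.
- *That 3.69–5.02 is a controlled effect.* The Background calls it a mean difference without naming the comparator.
- *That 5.23 is stated to be uncontrolled.* The document does not use that word; only its within-patient use is clear.

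**Conclusion.** The point holds as a moderate one. The closing paragraph of Section 3.12 contradicts itself on the expected FMA-UE change, and its 13–14 total adds a quantity that the protocol treats elsewhere as within-patient. The numerical correction is small, about 0.2 to 1.5 points on the alternatives available in the protocol. The larger issue is interpretive. With no BCI effect and a gain of 8.3, the only named test for change over time would be significant in roughly 54% to 100% of trials at n = 12 for SDs from 12 down to 3.4.

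Those rates assume normally distributed changes, an SD the documents do not supply, no FDR correction, and that 8.3 applies over the interval tested. The primary feasibility outcomes and the planning of the future trial are unaffected.

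**What to change.** Both changes belong in Section 3.12.

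**(a) Expected gain.** Label 5.23 as a within-patient change from mainly chronic stroke that is neither the change expected in this cohort nor an increment over standard care. Then drop 13–14, or rebuild it from a between-group effect: about 12.3 with the 4-point planning difference, or about 12.0–13.3 with 3.69–5.02 if that range is confirmed to be versus control. State the period over which the 8.3 accrued.

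**(b) Basis for efficacy statements.** Say that the Wilcoxon pre–post results describe change over time. Rest any statement about clinical efficacy on the matched-control comparison already planned in the Discussion: the difference in FMA-UE change over a comparable interval, with a 95% confidence interval. Section 3.3 describes control FMA-UE at baseline and discharge, so the interval used for both groups needs to be stated. Report the contrast as exploratory, given the unequal therapy dose and the historical controls.

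**Cost.** A few sentences and one contrast on controls that are already being matched. The sponsor gives up a more favourable expected figure and accepts a weaker, imprecise efficacy statement, since about 12 patients against historical controls will give a wide interval.

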### 3.13. Safety Monitoring

The Principal Investigator will be responsible for ensuring participant safety on a daily basis. Adverse events will be monitored during every session and throughout the study period of 24 weeks. Serious adverse events (SAEs) include death, life-threatening events, events requiring hospitalization or prolonging existing hospitalization, events resulting in persistent or significant disability, events requiring intervention to prevent permanent impairment, and other medically important events. All SAEs will be reported to the Institutional Review Board per reporting requirements.

**Potential Risks:** Physical risks include skin reactions or transient discomfort to FES pads or EEG headcaps and EEG gel and the theoretical possibility of triggering seizures or computer-related eye fatigue. Additional physical events relevant to acute stroke rehabilitation that will be actively monitored include aggravation of upper limb spasticity, hemiplegic shoulder pain, autonomic symptoms, and falls. Psychological risks include patient fatigue, anxiety or emotional distress, and sleep disturbance, which will be mitigated by allowing breaks between trial blocks and maintaining flexibility in session scheduling.

In recognition that the events listed above are not exhaustive of the adverse reactions relevant to acute stroke rehabilitation, systematic ascertainment of the following will be added to a standardized adverse-event case report form completed at every session and at each follow-up: aggravation of upper limb spasticity (change in Modified Ashworth Scale from baseline), hemiplegic shoulder pain (numeric or visual analogue scale with clinical examination), anxiety or emotional distress (a brief distress screen, with escalation to formal assessment as indicated), sleep disturbance, autonomic symptoms, falls, and fatigue. Each event will be recorded with its onset, severity, duration, relatedness to the intervention (graded unrelated, unlikely, possible, probable, or definite), action taken, and outcome. Serious adverse events will be defined per International Council for Harmonisation Good Clinical Practice criteria (death; life-threatening events; hospitalization or its prolongation; persistent or significant disability or incapacity; or other medically important events) and reported to the SingHealth Centralised Institutional Review Board within the mandated timelines using the board’s serious-adverse-event reporting forms, with parallel notification of the Principal Investigator and the study sponsor; an independent clinician not involved in intervention delivery will adjudicate the relatedness of all serious events. Recognizing that many clinically important events in this population are systemic rather than device-related, non-BCI-specific adverse events—recurrent stroke, seizures, sepsis, cardiac events, venous thromboembolism, autonomic dysfunction, and neuropsychiatric symptoms such as depression and anxiety—will additionally be ascertained by review of each participant’s electronic discharge summary rather than via a separate dedicated checklist given resource constraints.

### 3.14. Ethical Considerations

This study will be conducted in accordance with the ethical principles of the Declaration of Helsinki and consistent with Good Clinical Practice (GCP) guidelines. The protocol has been approved by the SingHealth Centralised Institutional Review Board (CIRB) (#2024-3186) and mutually recognized by the National Health Group Domain Specific Review Board (DSRB). The trial will be registered on ClinicalTrials.gov prior to participant enrollment. Written informed consent will be obtained from all participants or their legal representatives prior to enrollment. Given that the study requires preserved cognition for active BCI participation, patients unable to provide informed consent due to neurological injury will be excluded. All study-related documents, data, and information will be kept strictly confidential. Data used in analyses will be anonymized without reference to specific participant names. All records will be retained for at least 15 years after study termination.

## 4. Discussion

This manuscript presents a prospective feasibility study protocol examining the implementation of BCI-based upper limb neurorehabilitation during the early subacute phase following stroke, with an integrated implementation science and economic evaluation [31,32]. The novelty of this study lies in addressing a key evidence gap by evaluating closed-loop BCI rehabilitation during the acute and subacute post-stroke period (2–12 weeks), when neuroplasticity is theoretically the greatest, whereas most prior BCI studies have focused on chronic stroke patients who have already plateaued after conventional rehabilitation [24]. Beyond assessing efficacy, it advances the field toward real-world clinical adoption by evaluating implementation within the acute inpatient rehabilitation setting, incorporating a preliminary cost analysis, and investigating EEG-based biomarkers of recovery to inform future adaptive, biomarker-guided BCI therapies.

We highlight the following limitations: Without a concurrent control group, any observed changes cannot be definitively attributed to the BCI intervention versus spontaneous recovery in the acute/subacute phase. This is a particularly important consideration in the 2–12-week window, when substantial spontaneous neurological recovery occurs and follows broadly predictable, proportional-recovery-type trajectories, making the separation of intervention-related gain from natural recovery intrinsically difficult in a single-arm design. To characterize and bound this confounder, we will (i) benchmark the observed FMA-UE and ARAT trajectories against the spontaneous-recovery estimates derived from the propensity-matched historical controls and from published early-recovery models, (ii) examine whether within-training electrophysiological change (ERD/ERS and decoding accuracy) tracks clinical change more closely than the passage of time alone would predict, and (iii) present sensitivity analyses that attribute conservative proportions of the observed gain to spontaneous recovery. These steps cannot substitute for a concurrent randomized control arm, which remains the definitive solution and is planned for the subsequent trial. The use of historical controls for economic evaluation introduces potential residual confounding. However, this study is intended as a pragmatic feasibility study that would in future support a larger study. The small sample size (*n* = 12) is appropriate for feasibility but limits precision, subgroup analysis, and generalizability, meaning that all findings are intended as hypothesis-generating to inform a future adequately powered trial. A specific consideration in this early phase is patient selection: motor imagery is attention-dependent, and the fatigue, reduced concentration, and medical instability that are common soon after stroke may limit who can engage with the paradigm. Determining which acute and early subacute patients can tolerate and reliably operate the BCI is therefore an explicit feasibility output of this study and will be used to refine eligibility criteria for a future definitive trial.

For transparency, we set out each principal limitation together with the specific design improvement it motivates for a future adequately powered study: (1) the single-arm design will be replaced by a randomized, concurrently controlled trial; (2) reliance on historical controls, with its residual and temporal confounding, will be addressed through prospective concurrent recruitment and, for the economic analysis, contemporaneous comparators; (3) the small feasibility sample will be superseded by a sample size formally powered on the FMA-UE minimal clinically important difference and the variance estimates generated here; (4) the unequal rehabilitation dose will be resolved by a time-equated active or attention-controlled comparator; (5) the 24-week within-trial horizon will be extended by the long-term Markov extrapolation and by the additional 12-month clinical follow-up; (6) the incomplete separation of stroke etiologies will be addressed by pre-registering etiology- and severity-stratified subgroup hypotheses; and (7) the exploratory electrophysiological biomarker and action-observation predictors identified here will be advanced as pre-specified candidate predictors of response. Collectively, these refinements define a clear translational pathway from the present feasibility study to a definitive effectiveness and cost-effectiveness trial.

The findings from this study will have several important implications. Clinically, demonstration of feasibility and safety will support the integration of BCI technology into early stroke rehabilitation pathways. The identification of MI-EEG correlates with clinical efficacy measures will inform early treatment-related plasticity effects. A comprehensive economic evaluation will inform preliminary justification of the additional device and set-up costs and efforts required. The preliminary economic data will help healthcare administrators and policymakers understand the potential value proposition of BCI technology in stroke rehabilitation to inform resource allocation decisions.

Finally, from a health-service and economic standpoint, a plausible future application lies in telemedicine and home- or community-based delivery. The scenario analysis modeling partial substitution and reduced supervision described above is a first step in this direction: remote or minimally supervised BCI rehabilitation, with tele-supervised set-up and remote monitoring of adherence, decoding performance, and safety, could substantially improve access and reduce per-session therapist and facility costs while extending assessment and follow-up beyond the inpatient setting. Establishing the feasibility, safety, and reliability of supervised inpatient delivery in the present study is a necessary precursor to evaluating such tele-rehabilitation models, which we identify as a priority for subsequent research.

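### Step (iii) of the spontaneous-recovery safeguards takes a share of the observed gain itself, so without an external anchor it cannot show that recovery explains the whole gain

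*Protocol article*

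**What the plan says.** The limitations paragraph of Section 4 (Discussion) accepts that a single-arm study at 2–12 weeks after stroke cannot readily separate treatment effect from natural recovery. It then sets out three steps. The first begins "To characterize and bound this confounder, we will (i) benchmark the observed FMA-UE and ARAT trajectories against the spontaneous-recovery estimates"; these estimates come from the propensity-matched historical controls and from published early-recovery models. The second asks whether electrophysiological change tracks clinical change. The third reads "iii) present sensitivity analyses that attribute conservative proportions of the observed gain to spontaneous recovery". The paragraph adds that the steps do not replace a randomized control arm and that findings are hypothesis-generating.

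Section 3.12 (Data Analysis) supplies the related machinery and figures:

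- Test: "non-parametric tests, including the Wilcoxon signed-rank test, will be employed for within-subject comparisons across time points", after false-discovery-rate correction, "with statistical significance set at alpha = 0.05".
- Local gain without BCI: "mean FMA-UE improvement from 29.1 to 37.4 points (+8.3 points) with standard rehabilitation".
- Assumed BCI effect: "mean change of approximately 5.23 points (standard error 0.70".
- Expected total: "BCI may yield an expected total improvement of approximately 13–14 points if effects are additive".

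The Background and Section 2.4 put the FMA-UE minimal clinically important difference (MCID) at 4–6 points. It serves there for context and planning, not as an efficacy decision rule.

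**The concern.** A bound on a confounder has to allow the confounder to explain everything. Step (iii) sets the amount attributed to recovery as a fraction of the observed gain, so the amount grows and shrinks with the result it is meant to challenge. A cohort that merely recovers as patients do on standard rehabilitation would still show a positive remainder after any share below 100%.

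The complaint is not that the article omits the values of the share; those can sit in a fuller document. It is that the base of the share is fixed as the observed gain, and choosing values below 100% would not repair that. At stake is how a secondary result is read. A table of positive remainders, offered as a bound, could stand beside a step (i) benchmark that shows no excess over controls.

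**Working it through.** **Inputs.** Gain on standard rehabilitation: 29.1 to 37.4 (Section 3.12). Assumed BCI effect: 5.23 points (Section 3.12). MCID: 4–6 points (Background, Section 2.4). Sample: 12 enrolled, 10 after dropout (Section 2.4).

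**The article's own figure.** 37.4 − 29.1 = 8.3, and 8.3 + 5.23 = 13.53. This reproduces the stated total of about 13–14 points.

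**The rule as written.** Let G be the observed mean gain and s the share attributed to recovery. The remainder for BCI is R = (1 − s) × G. If G > 0 and s < 1, then R > 0.

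| Share s | R if BCI adds nothing (G = 8.3) | R if effects add as expected (G = 13.53) |
|---|---|---|
| 25% | 6.2 | 10.15 |
| 50% | 4.15 | 6.76 |
| 75% | 2.1 | 3.38 |
| Correct remainder | 0 | 5.23 |
| Share that gives it | 100% | 8.3 / 13.53 = 61% |

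The right share differs between the two columns, and only an external recovery amount can tell the analyst which applies. A share set without one can err either way: 50% credits 4.15 points too many in the first column, and 75% credits 5.23 − 3.38 = 1.85 too few in the second.

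**What the rule can change.** The size of R against the MCID does move. R falls below a threshold m once s exceeds 1 − m/G:

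- G = 8.3: below 6 points at s > 28%, below 4 at s > 52%.
- G = 13.53: below 6 points at s > 56%, below 4 at s > 70%.

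**If a test against zero were run on the remainders.** Multiplying every change by one common (1 − s) keeps all signs and ranks, so the signed-rank p-value is fixed. The mean and standard error shrink together, so the t statistic is fixed too. In one simulated sample (n = 12, SD 6, mean gain 8.16), the remainder fell from 8.16 to 4.08, 0.82 and 0.08 at s = 0, 50%, 90% and 99%. The Wilcoxon p-value was 0.000488 each time. Shares that differ between participants would keep the signs but could alter the ranks. The article does not say that any such test is planned.

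**The rule after the fix.** R = G − c, where c is an external gain in points. With c = 8.3, R = 13.53 − 8.3 = 5.23 under the article's expectation, and 8.3 − 8.3 = 0 if BCI adds nothing. The tipping point is c = G.

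**The case against.** The strongest reply is that step (iii) does not stand alone. Step (i), in the same sentence, already compares the observed trajectories with external estimates and can contradict a BCI gain. This stands. It narrows the point to step (iii) and makes the fix largely a matter of tying (iii) to (i).

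Second, the article does not say that the share is one constant, that it stops short of 100%, or that it ignores external data. If the share were the matched-control gain divided by the observed gain, the mean remainder would equal that from subtraction. This also stands, which is why the point is conditional. But the text names no such anchor, and a share so defined is better stated in points.

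Third, a reader might infer that the step can never overturn any conclusion about BCI, or that it guarantees a significant result. The documents do not support that. The size of the remainder can fall below the MCID, and the signed-rank test is assigned to comparisons across time points, not to scaled remainders.

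Fourth, a reader might simulate a cohort with no BCI effect and see the test against zero reject often: about 62–99% of runs for n = 10–12 and assumed SDs of 6–10. Those rates come from the acknowledged single-arm pre/post design and would occur without step (iii). The fall to about 3–6% after subtracting 8.3 is built into data simulated with a mean of 8.3. Neither figure measures this defect.

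Lastly, the 8.3 points are an imperfect anchor. They combine standard therapy with spontaneous recovery, are not matched to the trial cohort, and carry sampling error. This stands and shapes the fix.

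**Conclusion.** The point holds in limited form. With a share below 100% that is not anchored externally, step (iii) leaves a positive remainder for BCI whenever the mean gain is positive, so it cannot show the gain to be fully explained by non-BCI recovery. On the article's own 8.3 points and no BCI effect, a 50% share leaves 4.15 points, inside the MCID range. This rests on algebra and needs no assumed SD. It does assume that the share is applied to the observed gain, as the text says.

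Severity is minor. Clinical efficacy is secondary (Section 2.5), step (i) supplies the informative comparison, and the article says plainly that attribution is not definitive. It would be wrong to conclude that the protocol plans a claim of BCI efficacy resting on step (iii).

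**What to change.** Restate step (iii) as a tipping-point analysis in absolute points, tied to step (i):

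- Subtract external gains from the observed FMA-UE change: the matched-control mean, published recovery-model estimates, and the cited 8.3 points with a range around it. State the interval over which each was measured.
- Report the residual with a 95% CI that allows for uncertainty in the external gain, for example by using SD²/n plus the squared standard error of the external gain as the variance. Report the number of points at which the residual reaches zero.
- Describe the 8.3 points as standard rehabilitation plus spontaneous recovery. Participants also receive standard occupational therapy (Section 2.6), so subtracting it addresses what the added BCI package contributes, including its extra therapy time.
- Do not present scaled observed gains as evidence of a BCI contribution.

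The cost is a sentence or two of wording and no new data collection. The downside is that the residual may be near zero and its interval wide. With n = 12 and an SD of 6 (the value assumed in Section 2.4 for the two-arm calculation), the half-width is 2.201 × 6/√12 = 3.8 points before any allowance for the external gain.
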